### 3.5 Inclusion criteria

- Age  $\geq$  6 months to <12 years
- Presentation with:
  - clinically uncomplicated disease
  - fever ( $\geq 37.5^{\circ}\text{C}$  aural) or history of fever within the previous 72 hours, and
  - a positive malaria slide for *P. falciparum* (mono or mixed infection) of any parasitaemia (Kinshasa only)
- Informed consent provided by patient or relative/legal guardian

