### 3.7.1 Uganda

A member of the trial team will then perform a rapid structured assessment to initially exclude any child with clinical symptoms or signs indicating the need for hospitalisation (an exclusion criterion). Children with uncomplicated febrile illness will be registered in the eligibility screening log.

In order to use resources efficiently, reduce wasted time for the caregivers and children, and limit the number of finger prick blood tests on children, a two stage process is proposed for the screening and enrolment of our study subjects.

First, caregivers or guardians of children who are potentially eligible will be approached by a member of the trial team to invite them to join a clinical trial and explain very briefly this may involve hospital admission for 1-4 days and extra blood tests. Caregivers could at this stage could 'opt out' or ask for more information.

If they agree or want more details then the member of the trial team would explain that the study would screen children for malaria using malaria RDT and a haemoglobin level (both are routine tests) and a RDT for G6PD deficiency (not a routine test).

All these would require a single 'finger prick' specimen. This would establish if they have malaria and a relevant inclusion criterion ( $Hb \geq 6$  g/dL) and their G6PD status. It is anticipated that this process will take approximately 5 minutes of explanation and up to approximately 10 minutes for the screening blood tests.

Once the caregiver/legal guardian agrees to **consider** entry into the study, we will conduct finger prick sample for the screening blood tests:

- Malaria RDT
- Hb concentration (HemoCue)
- G6PD status using the AccessBio RDT (CareStart®)

Following the results of these tests, we will know if a child is suitable to join the study. If so and the caregivers / guardians still wish to proceed, a patient information sheet and consent form will be given to the caregivers/guardians to read and ask questions.

A research team clinician will oversee the consent process and answer questions. The caregivers/guardians can either decline to join the study or sign the consent form to proceed to the more detailed prestudy enrolment assessment.

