### 3.7.2 Kinshasa

In Kinshasa, out-patients with fever present directly to the KIMORU unit where they are tested routinely for malaria by RDT, and have a Hb concentration measured. If they are RDT positive, a blood film is done and if positive, they receive standard antimalarial treatment.

When a study takes places at KIMORU, a study nurse talks to the waiting caregivers of the potential patients to inform them that a study is taking place. If a caregiver/legal guardian expresses an interest to join the study, then verbal consent will be obtained to perform:

- malaria RDT
- a malaria film if the RDT is positive
- Hb concentration (HemoCue)
- G6PD status using the AccessBio RDT and/or FST

After children are seen by the study doctor, and the inclusion and exclusion criteria confirmed, a study nurse will proceed with the informed consent process with the caregivers/legal guardian.

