### 3.8 Enrolment into the study

Once caregivers have signed the consent form to join the study, a study (randomisation) number will be given and the following study assessments will be done:

- History of current illness, past medical, family and drug histories
- Symptoms checklist
- Detailed physical examination
- Baseline methaemoglobinaemia (by oximetry)
- Finger prick sample for:
  - Hb and haematocrit (HCT) concentration
  - Malaria blood film (H0)
  - Blood film for reticulocyte count
  - Blood spots for
    - parasite genotype, molecular markers of resistance
    - gametocyte qPCR
- Venous blood for:
  - Full blood count & reticulocyte count (if a suitable machine is available)
  - G6PD enzyme activity by gold standard spectrophotometric quantitative assay
  - G6PD & CYP 2D6 genotyping
  - Routine biochemistry, including total & unconjugated bilirubin, LDH, haptoglobin and creatinine
  - PQ, lumefantrine and piperazine concentrations (on a subset)

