## 11.2 Analyses & analysis populations

All patients who received at least one dose of ACT and PQ/placebo will be included in the analysis. All analyses will be detailed later in a prospectively written analysis plan. Below is a summary.

The main strategy for analysis of the primary end point will be assessed by chi squared or Fisher's exact test, as appropriate, calculating the 95% CIs of the risk difference to see if ACT + SLDPQ has achieved non-inferiority in the G6PDd group. Logistic regression will be used to adjust for potential confounders. Non inferiority will be assessed on the whole data set i.e. combining data from both sites using the lower end of the 95% confidence interval. Other proportional data will also be analysed by chi squared or Fisher's exact test.

Continuous data (e.g. Hb, biochemistry, parasite counts) between two groups will be analysed by the unpaired 't' test, transforming the data, as needed.

All analyses will be two sided and a p value of < 0.05 is considered statistically significant.

We will examine factors that are associated with: (i) the development of profound / severe anaemia (logistic regression), (ii) parameters of Hb recovery (multiple regression). *A priori*, we will explore the relationships between Hb profiles in the following: (i) G6PD status (defined by genotype and by enzyme activity), (ii) any IBD vs. not, (iii) age <5 vs. age ≥5y, (iv) high biomass infections, assessed by microscopy and measured HRP2 concentrations, and (v) males vs. females. For these analyses, estimates and 95% confidence intervals (CIs) will be presented but not p values.

The PK data for PQ and cPQ will be analysed by non-compartmental analysis. The following PK parameters will be estimated:

- Cmax
- Tmax
- Clearance
- Half life
- AUC
- Vd

For lumefantrine and piperaquine, drug absorption kinetics will be modelled over the first 24 hours.

The Day 7 concentrations of lumefantrine and piperaquine will be compared between PQ and placebo recipients. Depending on the lumefantrine and piperaquine data obtained, other modelled PK parameters will be determined, as the data permit.

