## 17 APPENDIX 1: STUDY SCHEDULE – KINSHASA & UGANDA INPATIENTS

| Initial patient management                                                                           |   |    |    |      |    |    |    |    |     |     |     |     |     |     |     |     |    |     | Blood volumes |      |     |     |      |  |  |  |
|------------------------------------------------------------------------------------------------------|---|----|----|------|----|----|----|----|-----|-----|-----|-----|-----|-----|-----|-----|----|-----|---------------|------|-----|-----|------|--|--|--|
|                                                                                                      |   |    |    |      |    |    |    |    |     |     |     |     |     |     |     |     |    |     | total         |      |     |     |      |  |  |  |
| Verbal consent (routine in DRC)                                                                      | X |    |    |      |    |    |    |    |     |     |     |     |     |     |     |     |    |     |               |      |     |     |      |  |  |  |
| Brief history & examination                                                                          | X |    |    |      |    |    |    |    |     |     |     |     |     |     |     |     |    |     |               |      |     |     |      |  |  |  |
| Hb (HemoCue)                                                                                         | X |    |    |      |    |    |    |    |     |     |     |     |     |     |     |     |    |     | 0.02          | 0.02 |     |     |      |  |  |  |
| Malaria RDT                                                                                          | X |    |    |      |    |    |    |    |     |     |     |     |     |     |     |     |    |     | 0.02          | 0.02 |     |     |      |  |  |  |
| Malaria blood film (Kinshasa only if malaria RDT positive)                                           | X |    |    |      |    |    |    |    |     |     |     |     |     |     |     |     |    |     | 0.05          | 0.05 |     |     |      |  |  |  |
| G6PD RDT qualitative                                                                                 | X |    |    |      |    |    |    |    |     |     |     |     |     |     |     |     |    |     | 0.02          | 0.02 |     |     |      |  |  |  |

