### Adequate clinical and parasitological response (ACPR)

- Absence of parasitaemia on day 42, irrespective of axillary temperature, in patients who did not previously meet any of the criteria of early treatment failure, late clinical failure or late parasitological failure.

The number of cases of **Total Treatment Failure (TTF)** is computed as ETF+LCF+LPF. After day 14 only parasitaemia confirmed by PCR as recrudescence is considered a treatment failure.

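### Ugandan children can enter on a positive RDT with a negative film, and the stated efficacy rules then misclassify them

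*Protocol*

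**What the plan says.** **Entry.** Protocol 3.5 asks for a positive slide with the qualifier "mono or mixed infection) of any parasitaemia (Kinshasa only". It lists no parasitological criterion for Uganda. The Ugandan test appears in 3.7.1, where "the study would screen children for malaria using malaria RDT and a haemoglobin level" describes the screening bloods (with a G6PD RDT), and then "Following the results of these tests, we will know if a child is suitable to join the study". No film comes before that decision. In Kinshasa (3.7.2) the order is different: "If they are RDT positive, a blood film is done and if positive, they receive standard antimalarial treatment". Appendix 1 agrees, since its screening row reads "Malaria blood film (Kinshasa only if malaria RDT positive". The screening rows for Ugandan outpatients in Appendix 2 show an RDT and no film.

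**After consent.** Section 3.8 takes a baseline film, "Malaria blood film (H0", in every enrolled child. No rule says what follows if it is negative.

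**Analysis.** Section 11.2 states: "All patients who received at least one dose of ACT and PQ/placebo will be included in the analysis". Appendix 3 defines adequate response as "Absence of parasitaemia on day 42, irrespective of axillary temperature" in patients with no earlier failure, and sets no condition on D0 parasitaemia. The same appendix makes D2 parasitaemia above the D0 count an early failure. After D14 it counts only PCR-confirmed recrudescence as failure.

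**The concern.** The trial's aim and design concern acute uncomplicated P. falciparum malaria. Parasite clearance and D42 cure are secondary objectives (2.2), and both presuppose a measurable baseline infection. One site confirms that infection by microscopy before entry and the other does not, yet all dosed children go into one analysis with one outcome definition. A child with no parasites seen at H0 has no clearance time or half-life, and the definition assigns that child a treatment outcome that mostly reflects the missing baseline count. At stake are the D42 cure estimate and the meaning of the clearance endpoints. The primary anaemia endpoint is a lesser matter.

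**Working it through.** **1. The protocol's own figure.** Inputs from 11.1: 1.5% event rate in both groups, margin 2.5%, two-sided alpha 0.05, power 80%.

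n = (1.960 + 0.842)² × 2 × 0.015 × 0.985 / 0.025² = 372 after rounding up, against 374 stated, so it reproduces to within two patients. 374 × 1.05 gives the stated 393.

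**2. A Ugandan child with a positive RDT and a negative H0 film, taken through the stated rules.**
- 3.5 and 3.7.1: eligible.
- 11.2: analysed once dosed.
- Appendix 3, D2: any parasitaemia exceeds a D0 count of zero, so the child is an early failure.
- Appendix 3, up to D14: parasitaemia meeting the late-failure rules can count as failure.
- Appendix 3, after D14: failure needs PCR-confirmed recrudescence, which is hard to show without a detectable D0 infection to match.
- Otherwise: adequate response.

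Misclassification can go either way, but most such children end as adequate responders.

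**3. Size for D42 cure.** Inputs:
- c, true cure in film-positive children: 92%. Section 12.3.1 gives more than 92% for AL; using 92% for both ACTs is an assumption.
- s, Ugandan share: 0.50 (assumed equal split), or at most 1200/1600 = 0.75 from the per-site ceiling in 11.1.
- f, film-negative share of Ugandan children: not in the protocol; 2% to 30% assumed.
- g, proportion of film-negative children classed as failures: 0 for the upper bound.

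With w = s × f, apparent cure = (1 − w) × c + w × (1 − g), so the overstatement is w × (0.08 − g).

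| s | f | w | Apparent pooled cure (g = 0) | Overstatement, points |
|---|---|---|---|---|
| 0.50 | 2% | 0.010 | 92.08% | 0.08 |
| 0.50 | 10% | 0.050 | 92.40% | 0.40 |
| 0.50 | 30% | 0.150 | 93.20% | 1.20 |
| 0.75 | 30% | 0.225 | 93.80% | 1.80 |

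For Uganda alone the apparent rate runs from 92.16% (f = 2%) to 94.40% (f = 30%). If g reached 8% the overstatement would vanish, and above 8% it would reverse.

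**4. The primary endpoint.** Film status at H0 is fixed before treatment, so film-negative children are expected equally in both arms. Suppose, as a limit, that they have no primary events. The 1.5% rate becomes 0.015 × 0.95 = 1.43% at w = 5% and 0.015 × 0.85 = 1.28% at w = 15%. Power at 374 per group is Φ(0.025 / √(2p(1 − p)/374) − 1.96), which moves from about 80% to 82% and 86%. The sample size is not undermined.

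Dilution does lean slightly towards non-inferiority. Under the same limit, let the true excess in film-positive children equal the margin (1.5% against 4.0%), and let w be the film-negative share of the G6PDd group:
- w = 5%: rates 1.425% and 3.80%, difference 2.375 points, standard error 1.163 points. Chance of declaring non-inferiority = Φ(0.125/1.163 − 1.96) = 3.2%.
- w = 15%: rates 1.275% and 3.40%, difference 2.125 points, standard error 1.102 points. Chance = Φ(0.375/1.102 − 1.96) = 5.3%.

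The nominal value is 2.5%. These are upper bounds, and they are the reason for a sensitivity analysis.

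**The case against.** **RDT entry in Uganda looks deliberate.** The stated aim is safety under near-routine conditions, and 3.7.1 treats the RDT as the test that establishes malaria. This stands, and enrolment need not change. It does not settle which children belong in a cure or clearance analysis.

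**An analysis plan could set the efficacy population.** Section 11.2 calls itself a summary, and nothing in it forbids an evaluable subset. That is fair. But the entry rule, the analysis population and the outcome definition are all stated in the protocol, and together they give the wrong classification. A later plan would have to narrow them.

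**Stronger readings that the protocol does not support:**
- A reader might infer that film-negative means uninfected, so that these children cannot fail. Section 7.1.2 calls a slide negative after at least 200 fields, which means parasites were not seen. Appendix 3 can also class such children as failures.
- A reader might infer that the H0 film goes unused. It starts the parasite series, 10% of D0 slides are cross-checked, and the D0 count is the reference for early failure. What is missing is a rule for a negative result.
- A reader might infer that cure is heavily inflated. The share is unknown, and even the zero-failure assumption keeps pooled inflation below 2 points.
- A reader might infer that the safety result is biased. Allocation is independent of baseline film status, so there is no bias by arm.

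**Conclusion.** The point holds for the secondary efficacy and clearance endpoints. As written, the protocol admits Ugandan children with a positive RDT and a negative film and keeps them in the analysis. It then classes most of them as adequate responders and any with D2 parasitaemia as early failures. Pooled cure is overstated by about 0.1 to 1.2 points with half the patients in Uganda, and by at most 1.8 points at the 75% ceiling. These sizes rest on an assumed film-negative share of 2% to 30%, a true cure rate of 92% and no failures in these children, so they are upper bounds for each share. The defect is modest but easily corrected. The sample size and the validity of the randomised primary comparison are not in question.

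**What to change.** 1. In 3.5, list the Ugandan entry criterion explicitly (a positive malaria RDT), matching 3.7.1.
2. In 11.2 and Appendix 3, limit the WHO efficacy outcomes (early failure, late failures, adequate response) and the parasite clearance measures to children at either site whose H0 film is positive for P. falciparum. Report how many children this leaves out, by site and arm.
3. Keep all dosed children in the primary safety analysis, and add one sensitivity analysis of the primary comparison in film-confirmed children.

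This costs some wording and one extra analysis on films already collected; enrolment and dosing do not change. The downside is a smaller Ugandan efficacy denominator and a slightly less favourable cure rate.

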### 3.6 Exclusion Criteria

The patient/subject will not enter the study if ANY of the following apply:

- Malaria danger signs, sign(s) of severe malaria, or decompensated anaemia, including:
  - An inability to take or retain fluids or oral medications
  - Confusion
  - Prostration
  - Convulsions
  - Respiratory distress
  - Passing of red or cola-coloured urine (putative “blackwater fever”)
- Hb <6 g/dL
- A comorbid illness that requires treatment in hospital (physician’s judgement)
- Patients on drugs known to cause haemolysis in G6PDd e.g. dapsone, nalidixic acid
- Known to be allergic to PQ, AL, or DHAPP
- Previous enrolment in the current trial or current enrolment in another trial

### 3.7 Initial assessment at outpatients or clinic

Potentially eligible children (i.e. children with a febrile illness) will be identified by the nurse or clinician on duty in outpatients in Uganda and at the KIMORU centre in Kinshasa and will be assessed for suitability for the study.

### 3.7.1 Uganda

A member of the trial team will then perform a rapid structured assessment to initially exclude any child with clinical symptoms or signs indicating the need for hospitalisation (an exclusion criterion). Children with uncomplicated febrile illness will be registered in the eligibility screening log.

In order to use resources efficiently, reduce wasted time for the caregivers and children, and limit the number of finger prick blood tests on children, a two stage process is proposed for the screening and enrolment of our study subjects.

First, caregivers or guardians of children who are potentially eligible will be approached by a member of the trial team to invite them to join a clinical trial and explain very briefly this may involve hospital admission for 1-4 days and extra blood tests. Caregivers could at this stage could 'opt out' or ask for more information.

If they agree or want more details then the member of the trial team would explain that the study would screen children for malaria using malaria RDT and a haemoglobin level (both are routine tests) and a RDT for G6PD deficiency (not a routine test).

All these would require a single 'finger prick' specimen. This would establish if they have malaria and a relevant inclusion criterion ( $Hb \geq 6$  g/dL) and their G6PD status. It is anticipated that this process will take approximately 5 minutes of explanation and up to approximately 10 minutes for the screening blood tests.

Once the caregiver/legal guardian agrees to **consider** entry into the study, we will conduct finger prick sample for the screening blood tests:

- Malaria RDT
- Hb concentration (HemoCue)
- G6PD status using the AccessBio RDT (CareStart®)

Following the results of these tests, we will know if a child is suitable to join the study. If so and the caregivers / guardians still wish to proceed, a patient information sheet and consent form will be given to the caregivers/guardians to read and ask questions.

A research team clinician will oversee the consent process and answer questions. The caregivers/guardians can either decline to join the study or sign the consent form to proceed to the more detailed prestudy enrolment assessment.

### 3.7.2 Kinshasa

In Kinshasa, out-patients with fever present directly to the KIMORU unit where they are tested routinely for malaria by RDT, and have a Hb concentration measured. If they are RDT positive, a blood film is done and if positive, they receive standard antimalarial treatment.

When a study takes places at KIMORU, a study nurse talks to the waiting caregivers of the potential patients to inform them that a study is taking place. If a caregiver/legal guardian expresses an interest to join the study, then verbal consent will be obtained to perform:

- malaria RDT
- a malaria film if the RDT is positive
- Hb concentration (HemoCue)
- G6PD status using the AccessBio RDT and/or FST

After children are seen by the study doctor, and the inclusion and exclusion criteria confirmed, a study nurse will proceed with the informed consent process with the caregivers/legal guardian.

### 3.7.3 Screening failure / caregiver decline

If the screening process finds that the patient is not suitable to join the study or the caregivers or guardians decline to join the study, the child will be treated for malaria according to local guidelines.

### 3.8 Enrolment into the study

Once caregivers have signed the consent form to join the study, a study (randomisation) number will be given and the following study assessments will be done:

- History of current illness, past medical, family and drug histories
- Symptoms checklist
- Detailed physical examination
- Baseline methaemoglobinaemia (by oximetry)
- Finger prick sample for:
  - Hb and haematocrit (HCT) concentration
  - Malaria blood film (H0)
  - Blood film for reticulocyte count
  - Blood spots for
    - parasite genotype, molecular markers of resistance
    - gametocyte qPCR
- Venous blood for:
  - Full blood count & reticulocyte count (if a suitable machine is available)
  - G6PD enzyme activity by gold standard spectrophotometric quantitative assay
  - G6PD & CYP 2D6 genotyping
  - Routine biochemistry, including total & unconjugated bilirubin, LDH, haptoglobin and creatinine
  - PQ, lumefantrine and piperazine concentrations (on a subset)

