#### 3.2 Study design

This is a randomised, multicentre, parallel-group safety trial of SLDPQ when combined with the first-line antimalarial therapy, AL, or DHAPP for treating acute uncomplicated *P. falciparum* malaria in G6PDd and G6PD normal African children. The trial is double blind with respect to SLDPQ but AL and DHAPP are open.

The trial will be stratified by G6PD status based on the results of a G6PD rapid diagnostic test (RDT)\*:

- a G6PDd group that will be randomised to AL or DHAPP plus SLDPQ or placebo, and
- a G6PD normal group that will be randomised to AL or DHAPP plus SLDPQ or placebo

\* we will use the AccessBio G6PD RDT. If a site also wishes, the fluorescent spot test (FST) can be used. Where there are discrepant FST RDT results, preference will be given to the FST.

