### 3.10 Drug allocation and randomisation

The study has four dosing groups for the G6PDds and four dosing groups for the G6PD normals:

- AL + SLDPQ

- AL + SLDPQ placebo
- DHAPP + SLDPQ, and
- DHAPP + SLDPQ placebo.

A computer generated randomisation list will be generated for each site:

- one list for G6PDd patients and
- one list for G6PD normal patients.

The treatment allocation will be placed in a sealed opaque envelope which will be opened after a study (randomisation) number is given. The treatment allocation will describe the ACT to be given and the number of the PQ/placebo pack.

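### The randomisation number is issued at consent, before the drug history and baseline assessments, and in Uganda no step before it covers the history-based exclusions

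*Protocol*

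**What the plan says.** Section 3.8 starts at signed consent: "a study (randomisation) number will be given and the following study assessments will be done". The list that follows includes "History of current illness, past medical, family and drug histories", a symptoms checklist, a detailed examination and a finger-prick Hb. Appendix 1 has the same row order, with the study number above the symptoms checklist.

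Section 3.10 puts the allocation in a "sealed opaque envelope which will be opened after a study (randomisation) number is given". On content it says: "The treatment allocation will describe the ACT to be given and the number of the PQ/placebo pack". Section 3.2 states: "The trial is double blind with respect to SLDPQ but AL and DHAPP are open". Opening the envelope therefore reveals AL or DHAPP but not SLDPQ or placebo.

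The sites reach consent differently. In Kinshasa (3.7.2) a study doctor sees the child and the entry criteria are confirmed first. In Uganda (3.7.1) the steps before written consent are a rapid assessment to screen out children who need admission, a malaria RDT, a HemoCue Hb and a G6PD RDT. Caregivers then "sign the consent form to proceed to the more detailed prestudy enrolment assessment".

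Section 3.6 also excludes "Patients on drugs known to cause haemolysis in G6PDd e.g. dapsone, nalidixic acid", known allergy to a study drug, and previous enrolment in this trial or current enrolment in another. Section 11.2 analyses children who received at least one dose of ACT and of PQ/placebo.

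**The concern.** Eligibility and baseline should be complete before anyone can learn the allocation. Here the stated order puts the number first and ties the envelope only to the number. Three things follow.

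- **Exclusions found after allocation.** A child found in Uganda to be on a haemolytic drug, or allergic, after the number is issued is either dosed or dropped. Section 4.5 classes wrongful inclusion as a violation, which it defines as potentially harmful. A child dropped before dosing is outside the 11.2 analysis set. Either way a numbered G6PDd allocation has been used.
- **Baseline recorded with the ACT known.** Section 8.1 counts an event as adverse if it is new or has worsened since baseline. If the envelope is already open, the baseline checklist can be coloured by knowing the ACT.
- **PK participation chosen with the ACT known.** Section 7.2 makes intensive PK sampling optional in Uganda and intends to compare PQ and cPQ exposure by ACT. A choice made after the ACT is known can select different children into the two ACT groups.

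**Working it through.** **1. Which criteria are settled before the number**

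| Criterion | Kinshasa (3.7.2) | Uganda (3.7.1) |
|---|---|---|
| Illness needing admission | before consent | before consent, rapid assessment |
| Malaria | before consent | before consent, RDT |
| Hb at least 6 g/dL | before consent | before consent, HemoCue |
| G6PD stratum | before consent | before consent, RDT |
| Haemolytic drugs | before consent | no step named; drug history is in 3.8 |
| Allergy to PQ, AL or DHAPP | before consent | no step named |
| Previous or other trial enrolment | before consent | no step named |

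Section 3.7.1 says suitability is known once the finger-prick results are back, but those tests cannot reveal drug use, an allergy or another trial. It also describes the assessment after consent as coming before the study, while 3.8 has already issued the number. The two sections need reconciling.

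**2. When the ACT can be known**

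The order in the text is consent, number (3.8), then envelope at any time after the number (3.10). Nothing requires the baseline assessments to be finished before the envelope is opened. Opening it before or after baseline would both comply.

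**3. Adverse event baseline**

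Section 8.3 treats events arising after screening and before randomisation as pre-existing. If issuing the number is randomisation, the 3.8 checklist and examination fall after that cut-off, so a symptom first noted there is not clearly baseline under 8.3. Section 8.1 starts the adverse event period at drug administration, whereas 8.3 documents events from inclusion. The interval between number and first dose is thus handled differently in the two places.

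**4. Does it threaten the sample size?**

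Inputs from 11.1: event rate 1.5% in both groups, margin 2.5%, two-sided alpha 0.05, power 80%.

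n per group = (1.960 + 0.842)² × 2 × 0.015 × 0.985 / 0.025² = 372 after rounding up. This agrees closely with the stated 374. The stated 393 is 374 × 1.05.

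The documents give no rate of exclusion between allocation and dosing, so the rate x below is assumed. With 800 / 2 = 400 per arm and the stated 5% loss, m = 400 × 0.95 × (1 − x), and power = Φ(0.025 / √(2 × 0.015 × 0.985 / m) − 1.960).

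| x (assumed, both sites) | m per arm | power |
|---|---|---|
| 0% | 380 | 80.9% |
| 1% | 376 | 80.5% |
| 2% | 372 | 80.1% |
| 5% | 361 | 78.9% |

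The table overstates the effect, because Kinshasa confirms all criteria before consent and x should apply to Uganda only. The site split is not given. Even at 5% across both sites, power falls by 2 percentage points.

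**The case against.** The strongest reply has four parts.

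- **Eligibility.** A reader might infer that Ugandan eligibility as a whole is decided after allocation. The text does not support that. The clinical pre-screen, malaria, Hb and G6PD status all come before written consent, and 3.7.3 deals with screening failures at that stage. Only the history-based exclusions, and any unexpected finding at the detailed examination, remain.
- **Number versus envelope.** Issuing a number does not reveal an allocation. Section 3.8 joins the number and the assessments without strictly ordering them, and 3.10.2 leaves the logistics to a separate guideline. This stands: opening before baseline is permitted, not prescribed. It does not remove the point, because the sequence as written allows the wrong order and only the protocol text can close it.
- **Primary comparison.** A reader might infer bias in the primary result. SLDPQ versus placebo is double blind, so knowing the ACT gives no route to different pre-dose drops between those arms. The endpoint rests on absolute Hb thresholds within 21 days, and a screening Hb exists beforehand. This stands.
- **Cross-ACT comparisons.** Section 11.2 sets out no AL-versus-DHAPP test, Day 7 partner-drug concentrations are compared between PQ and placebo, and the PK quotas in 7.2 are themselves set by ACT. This limits the exposure. However, 7.2 does plan PQ exposure by ACT, and adverse events and efficacy of both ACTs are secondary endpoints in 3.4.

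Wrongful inclusion is already reportable to the DMEC under 4.5. That records the event; it does not prevent it.

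**Conclusion.** The point holds in a limited form. The protocol issues the randomisation number at consent and lets the open ACT be revealed from then on. In Uganda, unlike Kinshasa, no prior step covers haemolytic drugs, allergy or other enrolment. Some ineligible children may be found only after allocation and, if not dosed, would disappear from the 11.2 set. Baseline symptoms and the Ugandan PK choice may be recorded with the ACT known, and symptoms recorded after the number fall outside the baseline window of 8.3.

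The exposed parts are any AL/DHAPP comparison, PQ exposure by ACT, the adverse event baseline and G6PDd allocations used up. The size cannot be derived from the documents. A reader might infer an underpowered trial; the calculation does not support that, since an assumed 5% loss at both sites moves power only from 80.9% to 78.9%. No shortfall is claimed.

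The verdict rests on two readings: that the number in 3.8 is the act of randomisation, as its name suggests, and that 3.7.1 lists all the Ugandan steps before consent.

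**What to change.** Reconcile 3.7.1, 3.8, 3.10 and Appendix 1 to one sequence for both sites:

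1. Screening tests and written consent, as now.
2. History including drug, allergy and trial-enrolment history, symptoms checklist, detailed examination, enrolment Hb and, in Uganda, the PK opt-in.
3. A recorded confirmation that every criterion in 3.5 and 3.6 is met. A child who fails here receives no number.
4. Randomisation number assigned.
5. Envelope opened immediately before dosing.

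The PK quotas by ACT can still be applied after step 5 among children whose caregivers have already agreed. With this order, the assessments in step 2 fall before randomisation, which also settles the baseline window in 8.3.

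The cost is wording in three sections and one appendix, plus the matching site procedure. It needs no extra tests, visits or staff.
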